## Abstract

**Background:**

Water requirements increases with gestational age. Insufficient water intake causes dehydration, which may adversely affect maternal health and birth outcomes. However, few related studies have been conducted. The purposes are to assess the water intake and hydration state among pregnant women, and to investigate the associations with pregnancy complications and maternal and infant outcomes.

**Methods:**

A prospective observational cohort study will be applied. A total of 380 pregnant women will be recruited from the First Affiliated Hospital of Hainan Medical University. Hydration biomarkers and health outcomes will be tested during 15~17 weeks’ gestation, 20~22 weeks’ gestation, 30~32 weeks’ gestation, during childbirth and 42 days after childbirth. Daily fluid intake will be collected using a *24-h fluid intake record for 7 consecutive days*. *A semi-quantified food frequency method* will be used to assess food intake and water intake from food. Anthropometric measurement will be taken following standardized processes. Intracellular fluid (ICF) and extracellular fluid (ECF) will be measured using a body composition analyzer. Morning fasting urine and blood osmolality will be tested by laboratory physicians using an osmotic pressure molar concentration meter. Pregnancy complications will be assessed and diagnosed throughout pregnancy and childbirth. Maternal-infant outcomes will be monitored using related indicators and technologies. In order to explore the internal mechanism and interactions from the perspective of endocrine, pregnancy related hormones (estradiol, prolactin, progesterone) and the hydration-related hormones (copeptin) will be tested during pregnancy. A mixed model of repeated measures ANOVA will be analyzed using SAS 9.2.

**Results:**

The results may provide basic data on water intake among pregnant women. The association between hydration state and maternal-infant outcomes will also be explored.

**Conclusions:**

This preliminary exploratory study findings will fill the gaps in the research on water intake, hydration and maternal health, birth outcomes, provide scientific reference data for updating recommendation on water adequate intake among pregnant women, and provide suggestion for developing water intake interventions.

**Trial registration:**

The protocol has been registered on the website of *Chinese Clinical Trial Registry*. The Identifier code is ChiCTR1800019284. The Registry date is 3 November, 2018. Registry name is “*Study for the correlation between hydration state and pregnancy complications, maternal and infant outcomes during pregnancy*”.

## Background

Water participates in a variety of physiological functions, and is essential for body development and survival [1–3]. Three sources of water input are available: drinking water, water from food and endogenous water. Four ways of water-output includes urine through urinary system, sweat through skin surface, breath through respiratory system, and feces through digestive system. Under normal conditions, water maintains a state of dynamic balance in body, that is, the amount of water-input is approximately equal to the amount of water-output [2, 3]. However, too much or insufficient water intake disturbs the dynamic water balance, changes the hydration state, and affects body health negatively. When water intake exceeds the regulatory capacity of kidney, it may cause acute water intoxication and hyponatremia. Insufficient water intake may induce a dehydrated state, which reduces cognition ability [4–6] and physical activity ability [7–10] and increases the risk of urinary system diseases (such as kidney stones, urinary tract infections and chronic kidney disease) [11, 12] and cardiovascular disease [13]. Therefore, maintaining an optimal hydration status is vital for human health.

During pregnancy, physiological changes cause daily water requirements to increase compared with people in normal physiological stages. Blood volume of pregnant women gradually increases from 6 to 8 weeks of pregnancy and reaches a peak at 32 to 34 weeks’ gestation. Water is the main component of human tissue, and 83% of blood is composed of water. Many changes occur in the urinary system: the kidneys become slightly larger; renal plasma flow and glomerular filtration rate increase in early pregnancy and remain at the high level throughout the whole pregnancy; and urine volume increases when being in the supine position and during the night [14]. Urination is the main mode of water output [15]. In the respiratory system, the ventilation increases by 40% /minute and the tidal volume increases by 39%, thus increasing the amount of water output through expiration. Under normal circumstances, approximately 500 mL of water per day is lost through sweating [15]. During pregnancy, water loss through sweating increases due to hyperactive adrenal and thyroid functions, an accelerated metabolism and increased cutaneous circulation. Nutrients and energy requirements for pregnant women are also increase, so food intake is increased. Water is the carrier of food metabolism, digestion, absorption, circulation and excretion. The water requirement is 1 mL for every 4.184 kJ of energy consumption, as much, more energy intake requires more water intake correspondingly [15, 16].

Surveys on fluid intake have shown that pregnant women have insufficient water intake. According to the data of the 1977–1978 Food Consumption Survey conducted by the US Department of Agriculture National, it was found that the average total water intake among 188 pregnant women was 2100 L/d [17]. In a study in New Zealand in 2014, the average daily water intake among 504 pregnant women was 2200 mL/d [18]. In a 2016 survey of 20 pregnant women, the average total water intake was almost 2259 mL/d [19]. In a 2016 study in Indonesia, the average daily water intake among 300 pregnant women was 2332 mL/d, although in approximately 42% of participants, the water intake was less than the recommended level (2048 mL/d) [20]. In China, only a few surveys on fluid intake among children and adults have been conducted. These studies have shown that only one third of the participants had adequate water intake and that almost one quarter of participants were dehydrated [21, 22]. However, no surveys has been conducted for water intake among pregnant women in China.

Changes occurring in the endocrine system during pregnancy may affect hydration. Prolactin begins to increase gradually at 7 weeks of pregnancy to promote mammary gland development for postpartum lactation. Aldosterone secreted by the outer globular band during pregnancy has a four-fold times. The secretion of estradiol at the end of pregnancy is 100 times greater than that in non-pregnant women [16]. Water balance is affected by various hormones. Insufficient water intake increases the secretion of vasopressin and aldosterone, which affects the water permeability of the distal renal tubules and collecting ducts. As a result, water reabsorption increases and water output decreases [23]. Copeptin, a stable peptide derived from the vasopressin precursor, is a potential predictor in various chronic diseases, such as diabetes insipidus and cardiovascular diseases [24]. Endocrine indexes related to hydration and pregnancy interact; thus, hydration state may be associated with pregnancy complications and maternal and infant outcomes.

Few studies have explored the associations of fluid intake and hydration state with pregnancy complications and maternal/infant outcomes. A prospective study in Italy involving 173 pregnant women revealed that total body water and intracellular and extracellular fluid in healthy pregnant women increased gradually throughout pregnancy, but an opposite trend was observed among women with gestational hypertension [25]. In a study conducted in Canada, the body compositions of 196 women 4 and 12 h postpartum were measured: the total body water of women without arterial hypertension was 44 L, whereas that of women with arterial hypertension was only 18 L [26]. This suggested that associations might exist between water retention and the development of hypertension. A US study showed that total body water may be a strong predictor of pre-eclampsia [27]. A Mexican study suggested that total body water in pregnant women with gestational hypertension and severed eclampsia was relatively higher than that in healthy pregnant women. In addition, chronic hypovolemia induced by insufficient water intake may be among the main risk factors in the development of diabetes [28], and higher intake of boiled water may reduce the risk of diabetes [29]. Data from the US Health and Nutrition Survey (2009–2012) showed that people without optimal hydration have a greater risk of obesity than those with optimal hydration [30], suggesting that hydration influences total gestational weight gain and postpartum weight retention. One study showed that the secretion of breast milk in lactating women increased with the amount of water intake [31]. A case–control study in the United States suggested that insufficient fluid intake was a risk factor for abortion requirements and preterm births, as well as low birth weight [32]. Other studies have shown that total body water has significant effects on birth weight [26, 33–36]. A US case-control study suggested that insufficient fluid intake was an independent risk factor of low birth weight [32]. In a randomized controlled trial in California, among 40 women with normal amniotic fluid index at 28 weeks of gestation, the amniotic fluid index increased by approximately 16% in the water intervention group and approximately 8% in the control group [37]. The relationship between the state of hydration during pregnancy and the physical infant outcomes has not been fully valued and studied, so there are not so many related literatures. More studies are needed to be carried out to explore the associations between water intake, hydration state and on pregnancy complications, maternal-infant outcomes.

In order to promote enough water intake, it is necessary to propose recommendations on water intake for pregnant women. Only some countries or organizations have made specific recommendations on water intake for pregnant women: 2.7 L/d is recommended by the American Institute of Medicine and 4.8 L/d is advised by the World Health Organization (WHO) [15]. A survey of dietary guidelines in 84 countries revealed that only 8 countries had quantitative recommendations for fluid intake [38]. Of the four editions of *Dietary Guidelines* (1989, 1997, 2007, and 2016) released in China, the first two editions had no recommendation for fluid intake [39, 40]. In 2007, the recommended amount of daily fluid intake was 1.2 L/d for adults, but no recommendation was given for pregnant women [41]. In 2016, the recommendation was 2.7 L/d for women and 3.0 L/d for men and pregnant women [15]. However, the recommendation for water intake for pregnant women was based on data of the water intake survey among pregnant women in other countries, not the data in China. Water requirements vary among pregnant women in different countries due to differences in dietary pattern, environment, and other factors; thus, it is necessary to undertake studies related to water intake during pregnancy in China.

Two hypotheses are proposed in this study: one is that some pregnant women are dehydrated due to having insufficient water intake and the other is that dehydration has negative effects on pregnancy and maternal and infant outcomes. The objectives of this study are, firstly, to investigate the fluid intake among pregnant women, secondly, to assess their hydration state, and finally, to investigate the associations with pregnancy complications and maternal-infant outcomes. This preliminary exploratory study on will provides some related reference data for updating the recommendation for adequate water intake among pregnant women. In addition, it will provide some evidences on water-related education. Based on this preliminary study, multicenter studies with larger sample sizes are required for the development of clinical guidelines and recommendations. The ultimate goals are to promote adequate water intake, to maintain optimal hydration state, and to improve mater health and birth outcomes.

## Methods/design

### Study hypotheses

One hypothesis is that a certain proportion of pregnant women have insufficient water intake and have risk of being in dehydration state. Another hypothesis is that dehydration state induced by insufficient water intake affects maternal health and birth outcomes.

### Study design

A prospective observational cohort study is designed. A total of 380 pregnant women with < 13 weeks’ gestation will be recruited. All items from the World Health Organization Trial Registration Data Set are shown in Table 1.

**Table 1 Tab1:** Items from the World Health Organization Trial Registration Data Set

Data Category	Information
Registration number	ChiCTR1800019284, Chinese clinical trial registry
Registration State	1,008,001 Prospective registration
Public title	Study for the correlation between hydration state and pregnancy complications, maternal and infant outcomes during pregnancy
Scientific title	The correlation between hydration state and pregnancy complications, maternal and infant outcomes during pregnancy
Approval of ethic committee	Ethical Review Committee of the Hainan Medical University
Ethical approval project identification code	2018–4
Date of approved by ethic committee	20 May 2018
Study type	Prospective observational study
Study design	Prospective observational study
Key inclusion and exclusion criteria	Inclusion criteria: Aged between 21~35; at first trimester of pregnancy (before 13 weeks), in health state, without metabolic disease, oral diseases, and so on. Exclusion criteria: Aged < 21, or age > 35; not being at first trimester of pregnancy (before 13 weeks); With metabolic disease, oral diseases, and other diseases.
Outcomes	Urine and blood osomolality, fluid intake, copeptin, pregnancy complications, maternal and infant outcomes
Collecting samples	Urine and blood
Recruitment state	Not initiated
Randomization Procedure (please state who generates the random number sequence and by what method)	Not applicable. A convenience sampling method will be used to recriute participants.

### Sample size calculation

For the calculation of sample size, the variable used is the incidence of new-onset hyperglycemia. Using the following formula, sample size is calculated:$$ {n}_1=\frac{\left(1+\raisebox{1ex}{$1$}\!\left/ \!\raisebox{-1ex}{$C$}\right.\right)\overline{p}\ \overline{q}{\left({U}_1-\raisebox{1ex}{$\alpha $}\!\left/ \!\raisebox{-1ex}{$2$}\right.+{U}_1-\beta \right)}^2}{{\left({P}_1-{P}_0\right)}^2} $$; *α* = 0.05, *β* = 0.20. Among these parameters, *p*_*1*_ = 20.9%, indicates the incidence of new-onset hyperglycemia among participants with insufficient fluid intake; *p*_*0*_ = 9.0%, means the incidence of new-onset hyperglycemia among participants with sufficient fluid intake; *c* = 4, indicates the ratio of pregnant women with water intake of > 0.5 L to pregnant women with water intake of < 0.5 L. These parameters were set based on the reference to the results of a related study [42]. A 10% dropout rate is taken into account to obtain the final sample size. For validity, 380 pregnant women will be needed.

### Participants

Pregnant women will be recruited from the First Affiliated Hospital of Hainan Medical University, Hainan province of China, using a convenience sampling method. The inclusion criteria are as follows: aged between 21 and 35 years; primigravidas; in the first trimester of pregnancy (before 13 weeks’ gestation); and without kidney diseases, diabetes mellitus, digestive system diseases, cardiovascular diseases and other diseases. The exclusion criteria are as follows: smoking; habitual consumption of alcohol (> 20 g/day) [43] or intensive physical activity; or with the diseases of kidney diseases, diabetes mellitus, digestive system diseases, cardiovascular diseases and other diseases.

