Preterm labor: It is defined as giving birth between 28 weeks’ and less than 37 weeks’ gestation. It will be diagnosed by obstetricians.

Mode of delivery: There are two modes: namely natural childbirth and cesarean section, which will be recorded by obstetricians.

Breast milk: The time for early initiation of breastfeeding will be recorded [66]. And the amount of breast milk will be evaluated based on the performances of infant after breast feeding.

Functional constipation: According to the Rome III criteria, it will be defined when participants present at least two of the following symptoms: at least one quarter of defecations for the last 12 weeks: lumpy or hard stools; straining; sensation of incomplete evacuation; sensation of anorectal obstruction; manual maneuvers to facilitate defecation; fewer than three defecations per week. Loose stools are rarely present without the use of laxatives [67]. Functional constipation will be diagnosed by obstetricians.

Total gestational weight gain (GWG) and postpartum weight retention (PWR): Both of them will be calculated based on weight of participants. GWG (kg) = weight before pregnancy (kg) -weight before delivery (kg). GWG will be assessed according to the recommendation of Institute of Medicine (IOM) [68]. PWR (kg) = weight before pregnancy (kg) - weight at 42 days after childbirth (kg).

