#### Infant outcomes

Infant birth weight and length: They will be measured using length and weight-measuring devices for infants (HLZ-20; Hualizheng, Tianjin, China) by professional obstetricians while infant is wearing light clothing. The scales for weight and length are calibrated at intervals of 10 g and 0.5 cm, respectively. Low birth weight for newborn infants is defined as a weight of < 2.5 kg, while macrosomia is defined as a weight of ≥4 kg. The growth of infant will be assessed according to the 2006 WHO Child Growth Standards [69].

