
There are both strengths and weaknesses for the design of the present study. Referring to strengths, first, to eliminate the potential confounding factors as much as possible, age, BMI, physiological state, sleep quality, food intake and physical activity will be evaluated and included as covariates in the statistical analyses. Second, fluid intake is dependent on environmental factors, such as temperature and humidity. The conduction of this study will be in Hainan, which is an area with a tropical monsoon climate. Thus, temperature and humidity will be recorded clearly to actualize the comparability among different studies in China and with those in other countries. Third, hydration state will be evaluated in many indicators, not only including urine osmolality, but also including body compositions (ICF and ECF), copeptin, fluid intake and blood osmolality. Fourth, water intake from food will be assessed in order to calculate total water intake. Fifthly, the prospective cohort design can avoid recall bias and improve the accuracy of the results. In terms of weakness, the mechanism about the associations of hydration with pregnancy complications, maternal and infant outcomes will not be studied comprehensively. In this study, only the endocrine mechanisms related to hydration and pregnancy will be explored. An observational study will elucidate the associations but is not necessary for the development of recommendations unless confounding factors are carefully controlled.

In summary, it is the first time to assess water intake and hydration stare among pregnant women, and it is the first time to investigate the associations of hydration with pregnancy complications, maternal and infant outcomes in China. Our results can provide some scientific reference data for updating the recommendations on fluid take for pregnant women and valuable evidence on the importance of hydration on maternal health during pregnancy. The results may also raise awareness on the importance of adequate fluid intake and optimal hydration in Chinese residents, especially pregnant women. More multicenter studies with larger sample sizes are required for the development of clinical guidelines and recommendations. The final goal is to develop water intake–related interventions to improve maternal health and birth outcomes.

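### Eligibility is not limited to singleton pregnancies and plurality is not a named covariate, so a few twin pregnancies can distort the birth-weight, preterm, weight-gain and hypertension analyses

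*Protocol article*

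**What the plan says.** **Eligibility.** The Participants section of the protocol article states its inclusion list outright: "The inclusion criteria are as follows: aged between 21 and 35 years; primigravidas; in the first trimester of pregnancy", followed by freedom from listed and other diseases. Its exclusions begin "The exclusion criteria are as follows: smoking; habitual consumption of alcohol (> 20 g/day) [43] or intensive physical activity" and end with the same diseases. Table 1 (Study design) gives a shorter version: "Exclusion criteria: Aged < 21, or age > 35; not being at first trimester of pregnancy (before 13 weeks", plus disease. Neither list mentions the number of fetuses. Primigravida limits the number of pregnancies, and a healthy twin pregnancy is not naturally one of the other diseases.

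**Outcomes.** Under Infant outcomes, "Low birth weight for newborn infants is defined as a weight of < 2.5 kg", which is a definition per newborn. Preterm labor is defined as "giving birth between 28 weeks’ and less than 37 weeks’ gestation". Gestational weight gain and postpartum weight retention are calculated in kilograms, and "GWG will be assessed according to the recommendation of Institute of Medicine (IOM". Gestational hypertension and preeclampsia are also outcomes.

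**Adjustment.** The Discussion names the variables meant to deal with confounding: "age, BMI, physiological state, sleep quality, food intake and physical activity will be evaluated and included as covariates in the statistical analyses". Plurality is not among them, and the article mentions twins or singletons nowhere.

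**The concern.** Twin infants are lighter and born earlier for reasons unrelated to maternal hydration. Plurality also bears on weight gain and blood pressure. The study wants to attribute differences in these outcomes to hydration state. Low birth weight is uncommon in singletons, so a few twin pregnancies can make up a visible part of all events. If they fall unevenly over the hydration groups, they can produce an apparent association or hide a real one, and no named covariate would absorb it. The article itself says that observational results need careful control of confounding before they can support recommendations.

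**Working it through.** **The plan's own figure.** The article gives no figure for plurality. Its sample size comes from new-onset hyperglycemia:
- Weighted mean incidence: (0.209 + 4 × 0.090)/5 = 0.1138.
- n₁ = 1.25 × 0.1138 × 0.8862 × 7.849/0.119² = 69.9, rounded to 70. The total is 5 × 70 = 350.
- A 10% dropout allowance gives 350 × 1.10 = 385 or 350/0.90 = 389, close to the stated 380. A singleton rule leaves this calculation unchanged.
- After 10% dropout, 380 × 0.90 = 342 women remain. The shares below are the same for 380 or 342.

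**Assumed inputs (none are in the documents).** Twin pregnancies t = 1–2%, with 3% as an upper case. Low birth weight: 50–60% of twin infants, 4–8% of singletons. Preterm birth: 50–60% of twin pregnancies, 5–10% of singleton pregnancies.

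**Number of twin pregnancies.** 380 × t = 3.8 (1%), 7.6 (2%) or 11.4 (3%). The chance of at least one at t = 1% is 1 − 0.99³⁸⁰ = 0.978.

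**Twin share of events.** With N = 380, twin risk p_T and singleton risk p_S:

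share = k·N·t·p_T / [k·N·t·p_T + N·(1 − t)·p_S],

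where k = 2 when infants are counted and k = 1 when women or deliveries are counted.

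Two worked cases for low-birth-weight infants:
- t = 1%, p_T = 50%, p_S = 6%: 3.8/(3.8 + 22.6) = 14%.
- t = 2%, p_T = 50%, p_S = 4%: 7.6/(7.6 + 14.9) = 34%.

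| Outcome | 1% twins | 2% twins | 3% twins |
|---|---|---|---|
| Low-birth-weight infants, mid-range pairings | 14–20% | 25–34% | 34–44% |
| Low-birth-weight infants, every combination | 11–23% | 20–38% | 28–48% |
| Women with a low-birth-weight infant, every combination | 6–13% | 11–23% | 16–32% |
| Preterm births, mid-range pairings | 5–9% | 9–17% | 13–24% |
| Preterm births, every combination | 5–11% | 9–20% | 13–27% |

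The mid-range pairings (singleton risk first) are 4%/50%, 6%/50% and 5%/60% for low birth weight, and 5%/50%, 7%/50%, 10%/50% and 7%/60% for preterm birth.

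**What an uneven spread does (illustration).** Borrow the 4:1 ratio from the sample-size section: about 68 against 274 of 342 women, with 7 twin pregnancies. That ratio refers to fluid intake; the hydration classes are three and their sizes are unknown. If twins fall at random, the smaller group holds none with probability 21% and three or more with probability 14% (hypergeometric). Take low birth weight in 4% of singletons and 50% of twin infants, with no hydration effect:
- Three twin pregnancies in the smaller group: (65 × 0.04 + 6 × 0.5)/71 = 7.9%, against (270 × 0.04 + 8 × 0.5)/278 = 5.3%. The ratio is about 1.5.
- None in the smaller group: 4.0%, against (267 × 0.04 + 14 × 0.5)/281 = 6.3%. The ratio is about 0.6.

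**Weight gain and weight retention.** These are measured in kilograms, so twins supply outlying values rather than events, unless weight gain is classified against the cited recommendation.

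**The case against.** **Condensed text.** This is a journal article, Table 1 is headed as key criteria and its inclusion entry trails off, and the two lists differ. A singleton rule might stand in a full protocol. Some weight is due to this. But the Participants section presents its list as the criteria, down to a gram threshold for alcohol, and eligibility is a protocol matter. A singleton-only analysis set could be left to an analysis plan, but that would be a repair of what eligibility lets in.

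**Chance, not bias.** Uneven spread by chance is part of sampling error, and confounding in the strict sense needs plurality to be associated with hydration state. The documents show no such association, so a reader who infers systematic bias goes too far. What stands is avoidable noise from a strong non-hydration cause.

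**Share of events.** A reader might infer that twins dominate every birth outcome. They do not. The large share belongs to low birth weight counted per infant; counted per woman, and for preterm birth, it is more modest.

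**Independence of twin records.** A reader might also infer that the planned logistic regression treats twin infants as independent, so that confidence intervals come out too narrow. The statistical analysis section names the method but no unit of analysis, sibling rule or variance estimator, so this cannot be asserted. The effect would be small anyway. Take 7 pairs among 349 infants with perfect within-pair correlation. For mean birth weight the variance ratio is (335 + 7 × 4)/349 = 1.04, about 2% in the standard error. For the low-birth-weight proportion, with the number of pairs fixed and risks of 4% and 50%, it is √[(335 × 0.04 × 0.96 + 28 × 0.25)/(335 × 0.04 × 0.96 + 14 × 0.25)] = 1.10, about 10%.

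**Importance.** The study calls itself preliminary and exploratory, and its size rests on hyperglycemia, which is not shown to be affected. At 4–8% there are only about 15–30 singleton low-birth-weight events in 380 women, so that analysis is imprecise in any case. This tempers the point without removing it.

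**Conclusion.** The point holds in limited form. As written, the criteria admit multiple pregnancies and no named covariate accounts for them, while several outcomes depend strongly on plurality. At assumed twin rates of 1–2%, some 4–8 of 380 women would supply roughly a seventh to a third of low-birth-weight infants and roughly a twentieth to a sixth of preterm births, with somewhat wider limits when all assumed rates are combined. In continuous outcomes they act as outliers. All rates are assumptions. The sample size is not affected, and neither systematic bias nor faulty standard errors can be read from the document. The change is worth making because it is cheap and removes a known non-hydration cause of uncommon events.

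**What to change.** Add singleton pregnancy to the inclusion criteria in the Participants section and in Table 1. If twins are already enrolled, or plurality becomes known only after enrolment, record it and restrict the analyses of birth weight, length, preterm birth, weight gain, weight retention, and gestational hypertension and preeclampsia to singletons.

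The cost is one line of text and about 1–3% of women: 3.8–11.4 of 380 at the assumed twin rates. At 2%, enrolling 380 singletons means approaching about 380/0.98 = 388 otherwise eligible women; restricting at analysis instead leaves about 335 of 342. The target of 380 need not change. The restricted results would apply to singleton pregnancies only, and the report should say so.
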